**Figure 3 f3:**
[figure not shown]
Graphical depiction of the set-up of the self-disclosure fMRI task.

At the end of the task, following the MRI scan, participants will be asked to disclose one of the items that they had chosen to share with their friend during the task. The item to disclose will be randomly chosen by the laboratory computer from a subset of items including both intimate and superficial items. Participants will be informed of this ahead of time. The first name of the friend is reported to check for consistency across waves, as well as their age. Finally, participants complete a short survey about the task (the Self-Disclosure Task Experience Survey, see **Supplementary file 1**).

##### This Is Me Task

Participants are asked to make a speech lasting one minute as if they are being interviewed for a new reality TV show. This video task was adapted from the High Risk Social Challenge (28), which is designed to measure social functioning under the stress of social evaluation in adolescents at high risk for developing schizophrenia. In contrast, *This is Me* minimizes the stressful and performative aspects of the speech for use in a typically developing child and adolescent population. Its instructions emphasize that the pretend show is interested in kids of all different backgrounds and types, suggests that participants describe themselves or talk about things that have happened to them, and allows participants up to two minutes to think about what they would like to say before recording. Speeches are videotaped. They are later transcribed for text analysis and coded by trained raters on a subset of items within the social-interpersonal (e.g., social anxiety and engagement) and affective (e.g., facial and nonverbal affect) factors identified from the High Risk Social Challenge ((28); the odd behavior and language factor is excluded and likely exists due to the task origin in a psychiatric context).

#### Diagnostic Interview

The Schedule for Affective Disorders and Schizophrenia for School Aged Children (6–18 Years) Present and Lifetime Version Interview (K-SADS-PL) will be administered as a measure of mental health symptomatology and as an assessment of current and past episodes of psychopathology according to DSM-IV criteria (29). Trained interviewers will administer the semi-structured interview to the adolescent, as well as a shortened interview to the parent/guardian (for report on the adolescent). The parent interview assesses family structure, physical health, medical history, treatment information, family history of mental illness, and autism spectrum disorder symptoms in the adolescent. These items are asked of the parent/guardian because it is expected they will have more information on these topics than the adolescent. The adolescent interview is composed of an introductory interview (including demographic information, school functioning, hobbies, and peer and family relations), and modules assessing present and lifetime history of the following psychiatric disorders: Depression, Mania, Psychosis, Panic Disorder, Agoraphobia, Specific Phobia, Separation Anxiety, Social Phobia, Generalized Anxiety Disorder, Obsessive Compulsive Disorder, Enuresis, Encopresis, Anorexia Nervosa, Bulimia Nervosa, and Post-Traumatic Stress Disorder. Detailed probes and a two- or three-point rating scale with anchors are provided for each criterion, and ratings are made for both current symptoms and symptoms during the most severe past episode. Information regarding the duration and number of episodes for each diagnosis is also collected. At the end of the interview, researchers will also assign a score of general functioning over the past two weeks, based on criteria outlined in the Children's Global Assessment Scale (30). At T1 participants were interviewed about current and lifetime symptoms, but at T2 and T3, they are asked to report only on symptoms since their last interview. Interviewers participate in weekly meetings to ensure adherence to interview administration guidelines, resolve diagnostic dilemmas, and decide on risk management procedures. For T1 20% of interviews were rated twice at the item level (screening items and supplemental items if supplement was completed). Interrater reliability was kappa = .81, which is considered to be in the ‘excellent range’ (29). For T2 and T3 a similar percentage of interviews will be rated twice for interrater reliability estimates.

In addition, self-harm will be examined in detail using an interview-format of the Deliberate Self Harm Inventory [DSHI; (31)] with adolescents. This interview will identify whether adolescents currently or previously engaged in self-harm, as well as the method and extent of engagement. Initial endorsement to intentionally engaging in different types of self-harm will be followed-up by more detailed questions regarding age of onset, frequency, last occurrence, total duration and hospitalization due to the behavior. Note that the DSHI was initially presented in questionnaire format (to the first 125 participants at T1), but this was changed to interview format to improve our ability to conduct risk management in case of self-harm endorsement. The questions remained the same.

#### Questionnaires

Adolescents and parents/guardians are both asked to report on the adolescent's puberty-related physical development, mental health, the family environment, and stressful life experiences. In addition, adolescents complete self-reports on their self-knowledge/self-perception, understanding of mental states, affiliation/self-disclosure, social functioning, and emotion regulation and understanding. See **Table 5** for the full list of questionnaires. All questionnaires are completed on an iPad using Qualtrics and automatically scored, except the Self-disclosure Task Experience Survey, which is completed on paper.

**Table 5 T5:** Questionnaire measures completed by parent/guardian and adolescent by topic.

Category	Reporter	Questionnaire	**T1**	**T2**	**T3**
Puberty	Adolescent	Pubertal Development Scale (PDS) (32)	✔	✔	✔
		Tanner Stage line drawings (33)	✔	✔	✔
	Parent	Parent-reported Pubertal Development Scale (PDS) (32)	✔	✔	✔
Mental health and behavior	Adolescent	Center for Epidemiological Studies-Depression Scale for Children (CES-DC) (34, 35)	✔	✔	✔
		Screen for Anxiety Related Emotional Disorders(SCARED-R) brief version (36)	✔	✔	✔
		Positive and Negative Affect Schedule for Children (PANAS-C) 10-item version (37)	✔	✔	✔
		Cognitive Appraisal of Risky Events - Revised (CARE-R) (38), adapted to focus on social outcome appraisal	✔	✔	✔
		Youth Risk Behavior Survey Middle School Version (YRBS-MS 2015) (39)	✔	✔	✔
		Pittsburgh Sleep Quality Index and Morningness-Eveningness Questionnaire Revised (PSQI-MEQ-R) (40, 41)	✔^1^	✔	✔
		Eating Disorder Inventory (EDI) (42)			✔
		Alcohol Use Disorder Identification Test (AUDIT) (43)			✔
		Cannabis Use Disorder Identification Test (CUDIT) (44)			✔
	Parent	Center for Epidemiological Studies-Depression Scale (CES-D) (45)	✔	✔	✔
		Child Behavior Checklist (CBCL)_(46)	✔	✔	✔
		Social Responsiveness Scale for Parents (SRS-P) (47)	✔	✔	✔
Risk factors and environment	Adolescent	Perceived Stress Scale (PSS) (48)	✔	✔	✔
		Childhood Trauma Questionnaire (CTQ) (49)	✔	✔	✔
		Multidimensional Scale of Perceived Social Support (MSPSS) (50)	✔	✔	✔
		Life Events Questionnaire (51)		✔	✔
		Community ladder [adapted from MacArthur Scale of Subjective Social Status; (52)]		✔	✔
	Parent	Demographics and Socioeconomic Status – updated (DEM-SES v2), see **Supplementary file 2**	✔	✔	✔
		Parenting Stress Index (PSI) short form (53)		✔	✔
		Family Adaptability and Cohesion Evaluation Scale (FACES-III) (54)		✔	✔
		Community ladder [adapted from MacArthur Scale of Subjective Social Status; (52)]		✔	✔
Self-knowledge and self-perception	Adolescent	Self-Perception Profile for Adolescents (SPPA) (55)	✔	✔	✔
		Self-Complexity Scale for Children (SCS-C) (56)	✔	✔	✔
		Revised Self-Consciousness Scale for Children (R-SCS-C) (57)	✔	✔	✔
		Child and Adolescent Mindfulness Measure (CAMM) (58)	✔	✔	✔
		Self-Concept Clarity Scale (SCC) (59)	✔	✔	✔
Understanding mental states	Adolescent	Reading the Mind in the Eyes (RMET) (60)	✔^2^	✔	✔
		Interpersonal Reactivity Index (IRI) (61)	✔	✔	✔
Affiliation and self-disclosure	Adolescent	Shulman Self-Disclosure Scale (SSDS) (62)	✔	✔	✔
		Co-Rumination Questionnaire (CRQ) (63)	✔	✔	✔
		Self-Disclosure Task Experience Survey (SDTES), see **Supplementary file 1**	✔	✔	✔
Social functioning	Adolescent	Intimate Friendship Scale (IFS) (64)	✔	✔	✔
		Big Five Inventory - 10 Item Version (BFI-10) (65)	✔	✔	✔
		Social Achievement Goals Questionnaire (SAQ) (66)	✔	✔	✔
		Social Reward Questionnaire - Child Version (K-SRQ) (67)	✔	✔	✔
		Fundamental Social Motives Inventory (FSMI) (68)			✔
		Relationship and Sexuality questions, see **Supplementary file 3**			✔
		Iowa-Netherlands Comparison Orientation Measure (INCOM) (69)			✔
		Adolescent Social Comparison Scale (ASCS) (70)			✔
Emotion regulation and understanding	Adolescent	Emotion Regulation Questionnaire (ERQ) (71)	✔	✔	✔
		Dweck's Implicit Theories Questionnaire (DIT) (72, 73)	✔	✔	✔
Well-being	Adolescent	EPOCH Scale (74)			✔
		Roberts UCLA Loneliness Scale (RULS-8) (75)			✔
		Satisfaction with Life Scale (76)			✔
		Utrecht Work Engagement Scale for Students (UWES-S) (77)			✔
		Flourishing Scale (78)			✔
Other	Adolescent	Edinburgh Handedness Inventory (EHI) (79)	✔	✔	✔
		Perceived Physical Health [shortened from (80)]		✔	✔
		Physical Activity Habits, see **Supplementary file 4**		✔	✔

^1^The PSQI-MEQ-R was added partway through T1.

^2^At T1, a shorter version of the RMET was administered (inadvertently, only the first half of the questions were included in Qualtrics).

The last three columns indicate if the questionnaire was administered at Time 1, 2, and 3, respectively.

#### Saliva for Hormones

Participants will be asked to collect four saliva samples of 2 ml each at home, in the weeks between the two laboratory sessions. Each sample will be provided through passive drool in the morning, directly after waking, one week apart, on a weekend day. This was done to account for shorter-term variations in the hormones and provide a more stable estimate of basal hormone levels, given that they fluctuate over the day and over the menstrual cycle. This was the preferred method (compared to e.g. sampling at a specific phase of the menstrual cycle) because menstrual cycles tend to be very irregular in early adolescence. Participants are instructed not to eat or brush their teeth before collecting the sample. Families will store the samples in their home freezer and bring it to their second lab session on ice in a cooler bag. Participants and their parents/guardians will be trained on how to collect and store the samples. They will record the time of day at collection and will report on illnesses and medication use in the 24 h before sample collection. Saliva samples are stored in a -80°C freezer in the lab until they are shipped (overnight on dry ice) to the Stress Physiology Investigative Team at the Iowa State University. There they are assayed in duplicate for dehydroepiandrosterone (DHEA), testosterone, and estradiol using Salimetrics Enzyme-Linked Immunosorbent Assay (ELISA) kits. Samples are rerun if the optical density coefficient of variation (CV) is greater than 7% and enough sample is left over to do so. All hormones for each participant are assayed on the same day to minimize freeze-thaw cycles. Moreover, all saliva samples from each participant are assayed on the same plate, to minimize variation in hormone concentrations that may be attributable to plate differences.

#### Saliva for Immune Factors

One additional 1.5 ml saliva sample is collected *via* the passive drool method at session 1 of every wave to examine immune markers. Participants are instructed not to eat or drink anything 30 minutes before collection. Samples are stored at -80°C until they are shipped on dry ice to an external laboratory: the Primate Assay Laboratory, University of California, Davis where samples are assayed in duplicate. Saliva samples are first centrifuged twice at 10,000 g at room temperature (24°C) for 10 min each time to remove cells and mucus, but are not diluted. Samples have a total of one freeze/thaw cycle. A multiplex bead array assay technology (Luminex, Millipore) is used to assay for C-reactive protein (CRP), interleukin(IL)-2, IL-4, IL-6, IL-10, IL-12_p70_, tumor necrosis factor alpha (TNF-α), interferon-gamma (IFN-ɣ) and secretory immunoglobulin A (SIgA) according to manufacturer's instructions.

#### Saliva for Telomere Length

At T1, a 2 ml saliva sample was collected *via* the passive drool method using DNA Genotek Oragene DISCOVER (OGR-500) collection devices during the second lab session to index telomere length. Participants were instructed not to eat, drink, chew gum, or smoke for 30 min before collection. At T2, a saliva sample for telomere length was collected from the first 109 participants completing this wave using the same instructions. Finally, participants who completed a saliva sample for telomere length during T1 will complete another one at T3. Samples are stored at room temperature until shipped for telomere assay by The Blackburn Lab (http://biochemistry2.ucsf.edu/labs/blackburn/) at the University of California San Francisco where samples are assayed in triplicate. This telomere length measurement assay is adapted from the published original method (81, 82). Using this method, the typical average CV is 3%–4%.

#### Hair

At each wave we will collect hair samples to examine DHEA, testosterone, and estradiol levels. Measuring hormones in hair is a relatively new technique, but it has proven to provide a reliable index of longer term levels (83). Five cm long samples will be taken from a 1cm-diameter section of hair (approximately 100 mg of hair), as close to the scalp as possible. Since hair grows about 1cm a month, this will provide an index of the hormone over the past five months. Samples are taken from the posterior vertex of the head, as this has proven to be the most reliable area to measure hormone levels, and it minimizes visibility. Hair samples will be assayed using ELISA in the same lab as the saliva samples.

In addition, participants fill out a brief survey about their hair texture and color; if they dye, bleach, perm, or straighten their hair; how often they blow dry their hair; how often they straighten their hair; and how they have treated their hair (washing, use of products and styling devices) in the days before the lab visit.

#### Anthropometrics

Height, weight, and waist circumference are measured to assess physical development. Measurements will be taken twice at each wave, once at the beginning of the second session and once at the end, to reduce measurement error. Height will be measured using a stadiometer and recorded in centimeters. Weight will be measured using a mechanical column scale with eye level beam and recorded in lbs. Participants are asked to remove shoes, coats and heavy clothing items. Waist circumference will be measured in centimeters using a flexible measuring tape directly on the skin, following the International Society for the Advancement of Kinanthropometry (ISAK) protocols.

#### IQ

Adolescents completed the Wechsler Abbreviated Scale of Intelligence, Second Edition [WASI-II; (84)] as a measure of intelligence. This was administered at T1 only; if for any reason it could not be completed at T1 (N = 19), it will be completed at the next possible wave. The two-subscale version is administered, including Vocabulary and Matrix Reasoning to obtain an estimate of full-scale IQ. This will mainly be used as a control variable in analyses.

### Data Analysis

To determine the sample size for the study, Monte Carlo power analyses were performed in Mplus, with each analysis using 1,000 replications, and an expected attrition rate of 10% per wave. At the time of writing, attrition was only 6.0% between T1 and T2 and 3% between T2 and T3. With the chosen sample size standardized direct effects of 0.235 or larger and moderating effects of 0.15 or larger have at least 80% chance of being statistically significant. For mediation analyses, standardized indirect effects of 0.09 or larger have greater than an 80% chance of statistical significance (assuming the standardized direct effects are at least 0.30).

The majority of data collected as part of the study will be uploaded to the Research Domain Criteria database of the National Institute of Health and will be freely available to other researchers: https://nda.nih.gov/edit_collection.html?id=2315. This includes all imaging data, salivary hormone data, most questionnaires, K-SADS-PL interview data, IQ, and anthropometrics.

Exact procedures used for processing and analysis of the data will depend on the aims and subset of data used in specific empirical papers. Scripts applied to run analyses will be placed on Github: https://github.com/dsnlab/TAG_scripts. However, preprocessing of the imaging data will follow standard pipelines, using fmriprep for fMRI data, freesurfer for structural MRI data, and FSL for diffusion MRI data. The self-evaluation fMRI task will be analyzed as an event-related design, so that both condition (“self” versus “change”) and adjective type can be modeled. The self-disclosure fMRI task will also be analyzed as an event-related design, so that both statement depth (“superficial” versus “intimate”) and choice (to share or keep private) can be modeled. Any region-based analyses will be supplemented with whole-brain or network-based analyses. When conducting null hypothesis significance tests we set our statistical thresholds to at least p < .05 while correcting for multiple comparisons, although the precise approaches to do so might vary between empirical papers as standards in the field continue to evolve (e.g., joint magnitude-extent thresholds for fMRI are now recommended to be set at a minimum of p < .001 for magnitude).

Standardized pipelines have also been developed for the processing of the hormone data. Both salivary and hair samples are assayed in duplicate (see the sections “Saliva for hormones” and “Hair”) and the mean of the duplicates will be used. Salivary hormone concentrations that are non-detectable and too low (i.e., left-censored) will be substituted using the following rules: 1) If other samples from the participant (i.e., from other sampling days) are also not detectable, the means of all samples are replaced with the lower limit of sensitivity (DHEA: 5 pg/ml; T: 1 pg/ml; E2: 0.1 pg/ml). 2) If other samples from the participant are detectable and 50% or more of the remaining samples are below the lower interval of the inter-quartile range (IQR) for the distribution, the mean of the non-detectable sample is replaced with the lower limit of sensitivity for that assay. 3) If other samples from the participant are detectable and less than 50% of the remaining samples are below the IQR for the distribution, the mean of the non-detectable sample is considered missing. For mean salivary hormone concentrations that were too high (i.e., right-censored), the following rules were applied: 1) If 50% or more of the remaining samples are above the upper IQR, the right censored sample is replaced with the upper limit of the standards for that assay (DHEA: 1000 pg/ml; T: 600 pg/ml; E2: 32 pg/ml). 2) If less than 50% of the remaining samples are above the upper IQR, the mean of the right censored sample is considered missing. Hair hormone concentrations (mean of the duplicates) that are non-detectable and too low, are substituted with the lower limit of sensitivity. Hair hormone concentrations that are non-detectable and right-censored are substituted with the upper limit of the standards for that assay. Hormone levels will be log-transformed to correct their non-Gaussian distribution.

General analytic strategies will include latent growth curve models to examine correlated change among the variables of interest (aims 1, 2, and 3) and mediation models (aim 4). The growth curve models will compare linear and quadratic change over time and dual-process growth models will model relationships among variables of interest over time. Mediating effects will be assessed using mediation models appropriate for longitudinal data, which account for confounds such as trait-stability as well as wave-to-wave autocorrelation. To assess significance of indirect (mediated) effects, we will use bootstrap procedures to construct empirical standard errors to account for the skewed sampling distribution of the indirect path estimate. Where relevant and possible, we will examine the impact of demographic variables (such as gender identity or socioeconomic status) on the investigated associations by comparing models with and without these variables.

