### Timeline and Procedure

This longitudinal study will take place over the course of approximately 3 years, and includes three testing waves. The first wave (T1) took place when participants were 10.0 to 13.0 years old (December 2015–March 2018, *M* age 11.64, *SD =* 0.81), the second wave (T2) took place approximately 18 months after T1 (July 2017–October 2019, *M* age 13.11, *SD =* 0.83), and the third wave (T3; currently underway) will take place approximately 18 months after T2. 163 participants completed T2 (retention rate of 94%), the average time between T1 and T2 was 1.57 years (*SD =* 0.12 years). At each wave participants will complete two laboratory sessions (each 2–3 h in length) 1 month apart, as well as a questionnaire and saliva sampling component at home (see *Measures*). Sessions were on average 33 days apart at T1 and 32 days at T2.

Parents/families who showed interest in the study were provided with information about the project and screened for eligibility over the phone. Those eligible were invited to the University of Oregon's Developmental Social Neuroscience laboratory. At the start of the first session parents/guardians provide written informed consent and children assent to participate. In the first session, participants complete a structured diagnostic interview and part of the questionnaires, and they receive instructions for saliva collection and preparation for the magnetic resonance imaging (MRI) scan (see *Measures* for more details on each component). At the end of the first session, adolescents and their parents/guardians are given the materials to complete saliva samples at home. Adolescents are asked to collect four saliva samples, one per week, between the two lab sessions. About a month later, participants complete the second session, including the MRI scan, the remaining questionnaires, the self-narrative video (*This is me task*), and hair sampling and anthropometric measures (see *Measures* for more details on each component). Procedures described in this paragraph are followed for all three waves, although some questionnaires were added in subsequent waves.

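### Hair hormone values outside the assay range are entered as the limit and modelled as if measured; if low values are common at T1, the rise of the lowest-starting girls is understated

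*Protocol article*

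**What the plan says.** Under Hair, the protocol article states: "At each wave we will collect hair samples to examine DHEA, testosterone, and estradiol levels". The timeline has three waves about 18 months apart, with one hair sample at each. Hair was obtained from 157 girls at T1 and 131 at T2.

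Under Data Analysis, hair concentrations "that are non-detectable and too low, are substituted with the lower limit of sensitivity". At the other end, "Hair hormone concentrations that are non-detectable and right-censored are substituted with the upper limit of the standards for that assay". Then "Hormone levels will be log-transformed to correct their non-Gaussian distribution".

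The saliva rules differ. With four samples per wave, an isolated low value can be dropped: where "less than 50% of the remaining samples are below the IQR for the distribution, the mean of the non-detectable sample is considered missing". Hair has no such branch, so every out-of-range value becomes a constant.

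The general strategy for the first three aims is latent growth curve modelling of correlated change. The article gives neither the share of hair samples outside the assay range nor hair-specific limits; the limits it lists stand within the saliva rules.

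**The concern.** A constant entered at the limit carries no mark that it is a bound rather than a measurement. A girl below the limit at T1 and T2 is recorded with no change between them. A girl who crosses the limit loses the part of her rise that lay below it. Taking logs afterwards does not restore it.

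The Background describes large hormone increases through puberty, and mean age at T1 was 11.64 years. Low-end censoring is therefore likely to be heaviest at T1, among girls who start lowest. Aim 1 concerns within-person hormone change, so the error falls on the quantity under study, and mostly on one part of the sample. The rule is fixed in the article as part of a standardized pipeline; it is not a detail left open.

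**Working it through.** **The study's own figure.** The article states no figure for hair non-detects. Its general power figure reproduces. With 10% attrition per wave, n = 174 × 0.9 × 0.9 ≈ 141. Fisher's z for 0.235 is 0.2395, and 0.2395 × √(141 − 3) − 1.960 = 0.853, which gives 80.3% power against the stated 80% or more.

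**Formula.** Let y0, y1, y2 be the log values at T1, T2, T3 and L the log limit. The recorded value is max(y, L). With three equally spaced waves the fitted linear slope is (y2 − y0)/2, so the slope lost per girl is [(L − y0)₊ − (L − y2)₊]/2, where (·)₊ is the positive part. For a normal variable with mean μ and SD σ, E(L − y)₊ = σ[φ(z) + zΦ(z)] with z = (L − μ)/σ.

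**Assumed inputs (none is in the article).** Intercept SD 0.8; residual SD 0.35; mean log rise per wave 0.4 (slope SD 0.3) or 0.6 (slope SD 0.4); true level-slope correlation 0; slope correlated 0.30 with an outside variable; 5-40% undetectable at T1.

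**Worked case: 20% undetectable, rise 0.4.**
- T1: σ = √(0.64 + 0.1225) = 0.873 and L = −0.8416 × 0.873 = −0.735. E(L − y0)₊ = 0.873 × (0.2800 − 0.1683) = 0.0975.
- T3: μ = 0.8, σ = √(0.64 + 4 × 0.09 + 0.1225) = 1.059, z = −1.449. E(L − y2)₊ = 1.059 × (0.1397 − 0.1068) = 0.0349.
- Slope lost = (0.0975 − 0.0349)/2 = 0.0313, and 0.0313/0.4 = 7.8%. The same steps with rise 0.6 give 6.0%.

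**Simulation of 400,000 girls, lower limit only.** Ranges span the two rise settings. The correlation comes from a linear growth model with equal residual variances.

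| Undetectable at T1 | Mean slope understated | Rise understated, lowest-starting quarter | Level-slope correlation (truth 0) |
|---|---|---|---|
| 5% | about 1% | 4-6% | see below |
| 10% | about 3% | 10-13% | 0.07-0.08 |
| 20% | 6-8% | 23-30% | 0.14-0.15 |
| 30% | 10-13% | 37-47% | 0.20-0.22 |
| 40% | 15-19% | 49-61% | 0.26-0.28 |

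A second set of settings (T1 SD 1, reliability 0.8-0.9, rise 0.3-0.5 SD per wave, slope SD 0.25-0.4) gave the same pattern. The lowest quarter lost 5-8%, 11-18%, 26-39% and 55-76% of its rise at 5%, 10%, 20% and 40%. The correlation was 0.03-0.07 at 5% and 0.12-0.26 at 20%.

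**How firm each result is.**
- Loss in the lowest quarter: essentially unchanged when the upper limit is also applied.
- Level-slope correlation: with residual variances free at each wave it is only 0.01-0.02 at 10% and 0.08-0.13 at 40%. With equal variances and both limits applied, it is −0.03 to −0.05 (10% low at T1, 10% high at T3), 0.02 to 0.04 (20% and 10%) and −0.07 to −0.12 (20% and 20%).
- Slope against an outside variable, lower limit only: at 40%, 0.231 falls to 0.214 (0.017/0.231 = 7.4%) and 0.257 to 0.244 (5.1%). At 20%, 0.230 falls to 0.224 (2.6%) and 0.254 to 0.249 (2.0%).

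**Does a censored model help?** In one simulated data set of 1,500 girls with 30% undetectable, the level-slope correlation was 0.30 after substitution, 0.09 from a left-censored likelihood and 0.05 from the uncensored data. At 10% the three were 0.05, −0.03 and −0.04.

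**The case against.** The strongest reply is that everything turns on a share the article does not give. At 5% undetectable the loss is small, and hair may be well within range. That stands, and it makes the point conditional.

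A reader might go further and infer that the growth model will show a false positive link between starting level and rise, so that more advanced girls appear to rise faster. The documents do not support this:
- The result changes with the residual specification and with the number of values at the upper limit, and it can shrink to near zero or turn negative.
- The true correlation is unknown. If it were −0.3, 20% low-end censoring would give about −0.13, which is attenuation and not an invented link.
- No aim names a hair hormone's starting level against its own slope. Aim 1 concerns covariation with brain measures, where the loss is modest.

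Nor does the article equate undetectable hair values with the least mature girls; the calculation concerns the lowest starting hormone levels.

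It can also be said that individual papers may choose their own processing and that a flag or sensitivity analysis may exist elsewhere. The article does allow such latitude in general. It nevertheless prints this rule as the standard pipeline, without a condition, and that printed rule is what is questioned here.

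**Conclusion.** The point holds in conditional form. Substituting the limit understates the rise of the lowest-starting girls when undetectable hair values are common at T1: by about 10-13% at 10%, 23-30% at 20% and 49-61% at 40% in the lowest quarter, with a mean-slope loss of about 3%, 6-8% and 15-19%. These sizes rest on the assumed shares and growth parameters above. At 5% or less the matter is minor.

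Distortion of the level-slope covariance is possible, but its sign and size cannot be read from the article. Correlations of the slope with outside variables lose at most about 8% from low-end censoring. This is a worthwhile refinement and does not threaten the main aims.

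**What to change.** 1. Keep a flag for every hair value at the lower limit or the top standard.
2. Report the share at each limit by hormone and wave. If it is no more than a few percent, that settles the matter.
3. Where the share is larger, fit the hair growth models with a censored-normal (Tobit) measurement model on the log scale, treating both limits as bounds. Alternatively, multiply impute within the limits from age, pubertal stage and the saliva values. Do this at least as a sensitivity analysis beside the substituted values.

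The cost is one change to the processing script and a censored-outcome option in the model, with longer run time and slightly wider intervals. Both approaches lean on log-normality beyond the limits, which the data cannot check. The censored model was tried here on 1,500 girls under a correctly specified model, not at the 131 with hair at T2, so its stability at study size should be checked. T3 was still underway at the time of writing, so the change could precede the final growth models.
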